## **Analysis plan:**

1. Test for non-inferiority of GI Genius CADx accuracy in white light against accuracy of expert endoscopists supported by virtual chromoendoscopy, having histopathology as a reference standard, with a margin of 10%.
2. Test for superiority of GI Genius CADx accuracy in white light against accuracy of non-expert endoscopists supported by virtual chromoendoscopy, having histopathology as a reference standard.
3. Test for non-inferiority of GI Genius CADx accuracy in white light against GI Genius CADx accuracy in virtual chromoendoscopy, having histopathology as a reference standard.
4. Report descriptive analysis of Sensitivity, Specificity, Accuracy, of GI Genius CADx optical characterization for different subdivision of lesion according to size, anatomical location, endoscope, age, sex, reason for colonoscopy.

## **Sample size:**

A previous pilot study involving GI Genius CADx on 60 patients, reported an accuracy of 85%. The sample size calculation is calculated assuming that experts can perform optical characterization with an accuracy of 87%. Using a one-sided alpha level of 0.025, a total of 480 lesions is required to achieve 80% power, which is increased by 5% to account for dropouts. The number of lesions for Standalone CADx study will therefore be 504.

CHANGE study plans to recruit 156 patients, which should correspond to about 500-800 lesions. Therefore, the first 504 lesions resected in CHANGE study, complete of a valid video recording and a valid histopathology outcome will be used for Standalone CADx study.

**Timeline:***CHANGE study*

Study registration on [clinicaltrials.gov](https://clinicaltrials.gov): May 12, 2021

First patient recruited: May 12, 2021

End of patient recruitment: July 2021

*Standalone CADx study:*

Study registration on [osf.io](https://osf.io): June 18, 2021

Email sent to first reviewers: June 21, 2021

End of study: September 2021

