| 
In order to assess GI Genius CADx performances in terms of prediction accuracy, the output of GI Genius CADx (adenoma/non-adenoma/no-prediction) will be evaluated against the histopathology reference standard (ground truth). The performances of GI Genius CADx will be compared against the prediction of the same lesions performed by a pool of endoscopists reviewing the video recording of the procedures blind to the histology results.
                                                                                                                                                                                                                                                                                                                                                                                                                                                                                                                                                                                                                                                                                                                                                                                                                                                                                                                                                                                                                                                                                                                                                                                                                                                                                                                                                                                                                                                                                                                  |

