**Study procedure:**

*Lesion collection*

Lesions used in the present study will be prospectively acquired in the clinical study named CHANGE. Patients enrolled will undergo a standard white-light colonoscopy with the support of the latest version of the CE-marked GIG CADx device (version 3.0.0). Colonoscopy will be performed according to the standard practice. The primary endpoint of CHANGE study is to measure the Negative Predictive Value (NPV) of GI Genius CADx optical diagnosis on diminutive ( $\leq 5$  mm) rectosigmoid polyps. CHANGE study estimated enrolment is of 156 participants, corresponding to a total of about 500-800 lesions. First valid 504 lesions resected in the CHANGE study will be included in the Standalone CADx study.

*Electronic data recording*

All endoscopy procedures in the CHANGE study will be recorded lossless (without image degradation or compression) and without any of the GI Genius markings from beginning to the end of the procedure. In other words, the video of the recorded procedures will bear no trace of the AI used. All clinical data of the participants and of the retrieved lesion will be recorded in an electronic CRF using openclinica ([www.openclinica.com](http://www.openclinica.com)).

*Batch subdivision*

For the Standalone CADx study, the following process will be used for video preparation. Every 84 consecutive lesions will be considered as an independent batch. Batches will be numbered in progressive order: batch01, batch02, etc. As soon as a batch is completed all video recordings in the batch will be prepared for lesion review. With this strategy, the review of the lesions via the website needed for the present study will be run in parallel to the acquisition of the patient in the CHANGE study.

*Videoclip check and annotation*

All video procedures from a given batch will be carefully examined by scientific annotator experts in the task of video preparation for artificial intelligence elaboration. In particular, the timing and the localization of each lesion in each patient of the batch will be carefully annotated and confronted with data of the lesion in the eCRF for the same patient, to avoid any possibility of erroneous correspondence between lesion in the video and following histology outcome. Lesions for which no recording is available will be excluded from Standalone CADx study.

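### The 480 lesions stated for 80% power do not follow from the protocol's own inputs; on the paired design a simple calculation needs at most 343, so the paragraph needs correcting

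*Protocol*

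**What the plan says.** All the inputs are in the Standalone CADx synopsis of the Protocol.

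- **CADx accuracy** (Sample size): "A previous pilot study involving GI Genius CADx on 60 patients, reported an accuracy of 85"%.
- **Expert accuracy** (Sample size): "assuming that experts can perform optical characterization with an accuracy of 87"%.
- **Alpha** (Sample size): "Using a one-sided alpha level of 0.025".
- **Result** (Sample size): "a total of 480 lesions is required to achieve 80% power, which is increased by 5% to account for dropouts", which leads to 504.
- **Margin** (Analysis plan, item 1): "with a margin of 10"%. The Sample size paragraph does not repeat it.
- **Pairing** (Background and Rationale): "The performances of GI Genius CADx will be compared against the prediction of the same lesions performed by a pool of endoscopists".
- **Lesions per patient** (Study procedure): "CHANGE study estimated enrolment is of 156 participants, corresponding to a total of about 500-800 lesions".

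The paragraph names no formula, no CADx-expert discordance, no design effect for several lesions per patient and no between-reader variance. The only stated adjustment is the 5% for dropouts.

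**The concern.** This paragraph is the only justification of the sample size for the sole primary endpoint. It presents 480 as the consequence of two accuracies, an alpha and a power, with the margin given one section earlier. A reader who puts those numbers into a standard non-inferiority formula does not get 480, whether paired or unpaired. The reader then cannot tell which alpha, which margin or which design was used. That matters for a non-inferiority result in a registered protocol, because the stated 80% is what others will use to judge how informative the comparison was meant to be.

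**Working it through.** **Inputs.** CADx accuracy 0.85, expert accuracy 0.87, one-sided alpha 0.025 and power 80% (Sample size); margin 0.10, read as absolute (Analysis plan). The expected difference is −0.02, so the distance to the margin is 0.10 − 0.02 = 0.08, squared 0.0064. The normal quantiles give (1.960 + 0.842)² = 7.849.

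**1. The protocol's figure.** 480 × 1.05 = 504, so the step from 480 to 504 is reproduced. (Dividing by 0.95 would give 506; the difference is trivial.) The 480 itself has to come from the inputs above.

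**2. Paired calculation, one fixed reader, independent lesions.** n = 7.849 × (ψ − 0.02²) / 0.0064, where ψ is the proportion of lesions on which exactly one of CADx and the reader is correct. The protocol gives no ψ, so I show the range.

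- Independent errors: ψ = 0.85 × 0.13 + 0.15 × 0.87 = 0.241.
- Largest possible: ψ = 0.15 + 0.13 = 0.28 (the two never err on the same lesion).

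| ψ | Lesions for 80% power | Power with 480 |
|---|---|---|
| 0.10 | 123 | >99.9% |
| 0.15 | 184 | 99.5% |
| 0.20 | 245 | 97.5% |
| 0.241 | about 295 | 94.7% |
| 0.28 | 343 | 91.2% |

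For this formula to return 480, ψ would have to be 480 × 0.0064 / 7.849 + 0.0004 = 0.392, above the 0.28 ceiling for a single reader.

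**3. Unpaired calculation.** n per group = 7.849 × (0.85 × 0.15 + 0.87 × 0.13) / 0.0064 = 7.849 × 0.2406 / 0.0064 = about 295, or about 590 in total.

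- 480 as the total (240 per group): 0.08 / √(0.2406/240) − 1.960 = 0.567, power 71%.
- 480 per group: 0.08 / √(0.2406/480) − 1.960 = 1.613, power 95%.

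Variants at one-sided 0.025 do not reach 480 either. Total sizes are 642 with continuity correction, 676 with the variance taken under the null, and 610 by Farrington-Manning. A one-sample test against 77% needs 157 to 198.

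**4. A calculation that does return 480.** Unpaired Farrington-Manning uses restricted accuracies of 0.7989 and 0.8989 under the null, with variance 0.7989 × 0.2011 + 0.8989 × 0.1011 = 0.2515. At one-sided 0.05, n per group = (1.645 × √0.2515 + 0.842 × √0.2406)² / 0.0064 = 239.4. That rounds up to 240, and 2 × 240 = 480. The simpler unpooled formula at 0.05 gives 466.

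**5. An allowance for clustering.** From 295 lesions, 480 needs a design effect of 480/295 = 1.63; from 343 it needs 480/343 = 1.40. With 504/156 = 3.23 lesions per patient, these imply intraclass correlations of 0.63/2.23 = 0.28 and 0.40/2.23 = 0.18. With 800/156 = 5.13 lesions per patient, they imply about 0.15 and 0.10.

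**The case against.** The best defence is that 480 may contain allowances that the paragraph does not mention. The single-reader ceiling of 28% discordance does not bind a comparison with a pool of at least 8 experts on several lesions per patient. Step 5 shows that unremarkable intraclass correlations would take the paired figure to 480. This stands as far as it goes: it cannot be said that no route leads to 480, nor that 80% is false for the full multi-reader, clustered design. It does not rescue the paragraph, which attributes 480 to the accuracies, alpha and power, and adds only the dropout inflation.

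A second defence is that the 10% margin is relative, which is 8.7 points of 87%. The distance to the margin is then 0.067. The paired formula gives 421 at independent errors and 489 at maximum discordance, so 480 would need ψ of about 0.275, with CADx and experts almost never wrong on the same lesion. The Analysis plan does not call the margin relative. If that was meant, the text must say so.

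A third objection is that variance components and multi-reader modelling usually belong in a statistical analysis plan, which is not shown here. That is accepted: their absence is not counted as a fault. What remains is a stated number that the stated inputs do not produce.

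Finally, the discrepancy is conservative for the simple paired test. That also stands, and it limits the severity.

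**Conclusion.** The stated pair of 480 lesions and 80% power is not reproducible from the protocol's inputs. On the paired design, with one fixed reader, independent lesions and an absolute 10-point margin, 80% power needs about 295 lesions at independent errors and 343 at most. The stated 480 exceeds that maximum by 137 and gives about 91% power or more. The unpaired total of about 590 misses 480 in the other direction.

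The match with an unpaired Farrington-Manning calculation at one-sided 0.05 is exact. If that is the source, it conflicts with both the stated 0.025 and the paired design. The documents do not show that it is, so it remains an inference.

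A reader might infer that the trial is underpowered. The documents do not support this. Only treating 480 as two independent groups of 240 gives less than 80% on the stated inputs, and the comparison is not of that kind. Between-reader spread could lower power for a claim about experts as a class, but every figure for it would be assumed. Suppose 8 experts with correlation 0.3 between them, CADx-expert correlation 0 to 0.3, and a design effect of 1.22 to 1.67. Power with 480 lesions is then 85–99% at a between-reader SD of 3 points, 76–92% at 5 and 63–78% at 7. None of these values is in the protocol, and the results fall on both sides of 80%. True power for the pool of experts cannot be settled from the document.

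This is a correction of a stated figure and leaves the conduct of the study unchanged.

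**What to change.** Keep the 504 lesions and the planned readers.

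1. Retrieve the calculation behind 480 and check it against the stated alpha of 0.025, the 10-point margin and the paired design. Say which formula was used and whether any allowance for clustering or readers was built in.
2. Replace the Sample size paragraph with a paired non-inferiority calculation that states the absolute margin of 10 points, one-sided alpha 0.025, both accuracies and the assumed CADx-expert discordance.
3. Restate the power that 480 evaluable lesions give in place of the bare 80%. Add a short sensitivity table over within-patient correlation and between-reader SD, with those values labelled as assumptions.

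The cost is one paragraph and a few hours of calculation. Lesions, readers, margin and test are unchanged.

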## STUDY SYNOPSIS

|                                                                                                                                                                                                                                                                                                                                                                                                                                                                                                                                                                                                                                                                                                                                                                                                                                                                                                                                                                                                                                                                                                                                                                                                                                                                                                                                                                                                                                                                                                                                                                                                                                                                                                                                                                                                                                                                                                                                                                                                                                                                                                                                                                                                                                                                                                                                                                                                                                            |
|--------------------------------------------------------------------------------------------------------------------------------------------------------------------------------------------------------------------------------------------------------------------------------------------------------------------------------------------------------------------------------------------------------------------------------------------------------------------------------------------------------------------------------------------------------------------------------------------------------------------------------------------------------------------------------------------------------------------------------------------------------------------------------------------------------------------------------------------------------------------------------------------------------------------------------------------------------------------------------------------------------------------------------------------------------------------------------------------------------------------------------------------------------------------------------------------------------------------------------------------------------------------------------------------------------------------------------------------------------------------------------------------------------------------------------------------------------------------------------------------------------------------------------------------------------------------------------------------------------------------------------------------------------------------------------------------------------------------------------------------------------------------------------------------------------------------------------------------------------------------------------------------------------------------------------------------------------------------------------------------------------------------------------------------------------------------------------------------------------------------------------------------------------------------------------------------------------------------------------------------------------------------------------------------------------------------------------------------------------------------------------------------------------------------------------------------|

| 1. Title of Study: CHANGE – Characterization Helping the Assessment of colorectal Neoplasia in Gastrointestinal Endoscopy                                                                                                                                                                                                                                                                                                                                                                                                                                                                                                                                                                                                                                                                                                                                                                                                                                                                                                                                                                                                                                                                                                                                                                                                                                                                                                                                                                                                                                                                                                                                                                                                                                                                                                                                                                                                                                                                                                                                                                                                                                                                                                                                                                                                                                                                                                           |
| 2. Study code: CHANGE                                                                                                                                                                                                                                                                                                                                                                                                                                                                                                                                                                                                                                                                                                                                                                                                                                                                                                                                                                                                                                                                                                                                                                                                                                                                                                                                                                                                                                                                                                                                                                                                                                                                                                                                                                                                                                                                                                                                                                                                                                                                                                                                                                                                                                                                                                                                                                                                               |
| 3. Clinical phase: post-marketing                                                                                                                                                                                                                                                                                                                                                                                                                                                                                                                                                                                                                                                                                                                                                                                                                                                                                                                                                                                                                                                                                                                                                                                                                                                                                                                                                                                                                                                                                                                                                                                                                                                                                                                                                                                                                                                                                                                                                                                                                                                                                                                                                                                                                                                                                                                                                                                                   |
| 4. Study design: Multi-center, single-arm, prospective study                                                                                                                                                                                                                                                                                                                                                                                                                                                                                                                                                                                                                                                                                                                                                                                                                                                                                                                                                                                                                                                                                                                                                                                                                                                                                                                                                                                                                                                                                                                                                                                                                                                                                                                                                                                                                                                                                                                                                                                                                                                                                                                                                                                                                                                                                                                                                                        |
| Investigational Medical Device (IMD): GI Genius CADx, software version 3.0.0                                                                                                                                                                                                                                                                                                                                                                                                                                                                                                                                                                                                                                                                                                                                                                                                                                                                                                                                                                                                                                                                                                                                                                                                                                                                                                                                                                                                                                                                                                                                                                                                                                                                                                                                                                                                                                                                                                                                                                                                                                                                                                                                                                                                                                                                                                                                                        |
| 5. Background and Rationale: 
Diminutive colorectal polyps (<math>\leq 5</math> mm) represent most of the polyps detected during colonoscopy, especially in the rectum-sigmoid tract. The characterization of these polyps by virtual chromoendoscopy is recognized as a key element for innovative imaging techniques. As a matter of facts diminutive colorectal polyps are very frequent and, if located in the rectosigmoid colon, they present a very low malignant risk (0.3% of evolution towards advanced adenoma and up to 0.08% of evolution towards invasive carcinoma). The real-time characterization would allow to identify the lowest risk polyps (hyperplastic subtype), to leave them in situ or, if resected, not to send them for histological examination, allowing a huge saving in healthcare associated costs.
 
Recently, the American Society for Gastrointestinal Endoscopy (ASGE) Technology Committee established the Preservation and Incorporation of Valuable endoscopic Innovations (PIVI) document, specific for real-time histological assessment for tiny colorectal polyps, to establish reference quality thresholds. Two performance standards have been developed to guide the use of advanced imaging:
 

1. for diminutive polyps to be resected and discarded without pathologic assessment, endoscopic technology (when used with high confidence) used to determine histology of polyps <math>\leq 5</math>mm in size, when combined with the histopathology assessment of polyps <math>> 5</math> mm in size, should provide a <math>\geq 90\%</math> agreement in assignment of post-polypectomy surveillance intervals when compared to decisions based on pathology assessment of all identified polyps;

2. in order for a technology to be used to guide the decision to leave suspected rectosigmoid hyperplastic polyps <math>\leq 5</math> mm in size in place (without resection), the technology should provide <math>\geq 90\%</math> negative predictive value (when used with high confidence) for adenomatous histology.

 
Computer-Aided-Diagnosis (CAD) is an artificial intelligence-based tool that would allow rapid and objective characterization of these lesions. The GI Genius CADx was developed to help endoscopists in their clinical practices for polyps characterization.
 |
| 6. Objective: 
Primary object of the study is to prospectively evaluate if GI Genius CADx output can achieve <math>\geq 90\%</math> Negative Predictive Value in characterization (i.e. as adenomas or non-adenomas) of diminutive rectosigmoid polyps (i.e. PIVI 2), having conventional histopathology analysis of the resected specimens as reference standard. An exploratory objective of the study is to assess if there is an agreement between the post-polypectomy surveillance intervals assigned by a combined use of GI Genius CADx as a means for optical diagnosis of diminutive (<math>\leq 5</math> mm) rectosigmoid polyps and conventional histology of polyps <math>>5</math> mm, and and those assigned by histology as unique means of diagnosis of all polyps (regardless of size or location).
                                                                                                                                                                                                                                                                                                                                                                                                                                                                                                                                                                                                                                                                                                                                                                                                                                                                                                                                                                                                                                                                                                                                                                                                                                                                                                                                                                                                                                                                                                                                                                                                      |
| 7. Study sites: 
Ospedale Nuovo Regina Margherita, Rome, Italy
                                                                                                                                                                                                                                                                                                                                                                                                                                                                                                                                                                                                                                                                                                                                                                                                                                                                                                                                                                                                                                                                                                                                                                                                                                                                                                                                                                                                                                                                                                                                                                                                                                                                                                                                                                                                                                                                                                                                                                                                                                                                                                                                                                                                                                                                                                                                                                |

